### Control group

Participating patients of the control group are also called by our research assistant to check the inclusion criteria and to register the answers to the CaFaSpA referral rule. No active advice regarding a referral takes place. If control group patients choose to go to their GP, they will be treated according to the Dutch College of General Practice guidelines for the management of low back pain [11].

Before the IMPACT study started we discussed with GPs the weaknesses and difficulties of our study design. We received feedback concerning the benefit of participating for GPs or patients who were randomized to the control group. It was feared that the lost to follow up would be great in the usual care group. To increase the feasibility of our study we decided to communicate the outcome of the referral rule to the control group after 4 months and thereby eliminating the contrast between the intervention and usual care group.

Therefore, four months after inclusion (after our primary outcome time point) the usual care CLBP patients and their GPs will receive a letter containing the outcome of the referral rule and an advice to refer or not refer the patient. After receiving the outcome of the referral rule the patients of the control group will be followed for two years, data will be collected after 1 and 2 years of exposure to the referral rule, this will be sixteen and twenty-eight months after inclusion of the study (Fig. 1).

**Fig. 1 Fig1:**
[figure not shown]
Flowchart of the IMPACT study

### Data collection

Data collection of patient outcomes are at baseline (T0) (directly after inclusion of a patient in the study), after 4 months (T1), after 12 or 16 months (T3) and after 24 or 28 months (T4) (Fig. 1). At each time point patients will automatically receive an email with a link to online questionnaires.

### Outcome measures

The primary clinical outcome is the score on the Roland Morris Disability Questionnaire (RMDQ) after 4 months [12]. The RMDQ is a patient reported outcome and has a scale of 0 to 24. A higher score indicates a more severe disability score. The advantage of using the RMDQ as primary outcomes measure is that it is applicable in all participants as all participants are suffering from low back pain complaints. While for instance the BASDAI is only validated to use in axSpA patients. In general, the outcomes measures can be divided into three categories:Patient reported outcomeso Disability measured by the Roland Morris Disability questionnaireo Pain measured by the Visual Analogue Scale (VAS) pain [13]o Health related quality of life measured by the SF-36 version 2 and EQ-5D [14, 15].o Disease activity for axSpA, measured by the BASDAI [16].o Neuropathic components related to back pain measured by the painDETECT [17]Processo Diagnosis of axial spondyloarthritis made by rheumatologists, which is verified by hospital records.Costso Loss of work-productivity measured by work participation (*i*MTA Productivity Cost Questionnaire iPCQ)) [18]o Health care resources use measured by the *i*MTA Medical Consumption Questionnaire [19]

### Compliance

The compliance of patients is optimized by sending up to three reminders emails, asking the patient to fill out the online questionnaires. If the patient still has not completed the questionnaires the research assistant will contact the patient by telephone and the questionnaires are sent to the patient by post.

### Sample size

For the power calculation we assumed a difference of 2.5 points on the RMDQ at four months between the referral rule and usual care group. These 2.5 points are the clinically significant difference, found in previous studies [20, 21]. The SD of the RMDQ is 6.0 based on data observed in the previous CaFaSpA 2 study [4]. Detection of this 2.5 point improvement in a randomized trial would require 180 patients per group, using a two-sided α of 0.05 and power of 0.80.

Patient in the intervention group who have a negative result of the referral strategy (i.e. no referral to the rheumatologist) will receive the same treatment as the usual care group. Therefore, the effect of the referral strategy can only be assessed in patients with a positive result of the referral strategy. From the previous CaFaSpA studies we know that around 50 % of the participating patients will have a positive result. Therefore 360 patients(180 *x*2)would be required for 80 % power.

Further, the sample size was adjusted for cluster randomization based on an intra-cluster correlation coefficient of 0.05 and an average cluster size of 16 [22]. [23] The average cluster size is based on data of the CaFaSpA 1 and 2 studies, with on average 16 participating patients per GP. With these findings we can calculate the design effect; design effect = 1 + (16–1) * 0.05 = 1.75

Multiplying 360 patients by the design effect of 1.75 implies that a total of 630 patients must be included in this study. If a lost to follow up of 25 % is taken into account 840 patients need to be enrolled. Assuming 16 CLBP patients per GP, implies that 54 GPs (840/16) need to be randomized (Fig. 2). We expect that 16 patient per GP practice will participate, if the number of participating patients per practice is smaller, for example only 6, this will lead to a smaller design effect (1.25) and a total of only 600 patients should be enrolled to create sufficient power.

**Fig. 2 Fig2:**
[figure not shown]
Sample size calculation taking clustering into account (ICC of 0.05)

### Data analysis

Effects at 4 months and the process evaluation will be analysed according to the intention-to-treat principle. The baseline characteristics of the patients will be summarized by randomisation group, reported as mean (standard deviation) or median (interquartile range) for continuous variables and count (percent) for categorical variables.

As this is a cluster-randomized trial mixed effect regression analysis will be used to compare the mean RMDQ score after four months between the intervention and usual care group. Fixed effects include allocation group and result of the referral strategy (referral y/n). As the effect of the referral strategy is expected in the subgroup of patient with a referral advice, an interaction term between allocation group and result of the referral strategy will also be included. A random intercept will be included adjusting for clustering [24, 25]. This random intercept stand for the effect of different primary care practices (i.e. clusters).

For the secondary outcomes we will again use a mixed effect regression analysis to estimate the effect of the use of the referral strategy after 4 months on process level (i.e. the number of axSpA diagnoses by a rheumatologists), pain (VAS pain), quality of life (SF-36 version 2 and EQ-5D) and disease activity (BASDAI). We will use linear regression for continuous outcomes and logistic regression for dichotomous outcomes. Similar to the primary outcome analysis an interaction term and random intercept will be used to take into account interaction between allocation group and referral strategy and clustering. We intended to assess the effect of using the referral strategy also at 12 and 24 months. However, patients in the control group receive also an advice based on the referral rule after 4 months. Contract between the intervention and control group is no longer present. Therefore, individual trajectories will be modeled using random effect regression with patient outcome as the dependent variable and time as covariate and a random intercept for patient.

For the cost evaluation we will compare costs before and after the application of the referral strategy. We will consider costs of provided health care and costs due to loss of work-productivity. In order to calculate costs, the volume of care will be linked to the actual, integrated cost prices per medical service [26].

A *p*-value of <0.05 will be considered statistically significant. Statistical analyses will be undertaken with STATA.

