### Randomisation, allocation procedure and blinding

Primary care practices are randomly allocated to either the intervention or the control group. Randomisation is stratified for number of GPs working in the primary care practice (one or two vs more than two) to ensure similar number of patients in both groups. The block randomisation schedule is computer generated and administrated by an independent person, who is not involved in patient care. It is impossible to blind patients or GPs for allocation. If a patient receives the advice of a referral to the rheumatologist, both the patient and the GP are actively involved in this referral. Also the outcome assessment is not blinded, as patients assess the outcomes themselves by filling in questionnaires. Blinded analyses of the data will take place when possible.

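### The primary model leaves out baseline RMDQ and the practice-size stratum, and so gives up precision and protection against chance baseline imbalance; the planned analysis is nonetheless valid

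*Protocol article*

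**What the plan says.** The endpoint is fixed under Outcome measures: "The primary clinical outcome is the score on the Roland Morris Disability Questionnaire (RMDQ) after 4 months". Under Data analysis, "mixed effect regression analysis will be used to compare the mean RMDQ score after four months between the intervention and usual care group". The model terms follow. "Fixed effects include allocation group and result of the referral strategy (referral y/n"), and "an interaction term between allocation group and result of the referral strategy will also be included". On the random part: "This random intercept stand for the effect of different primary care practices (i.e. clusters"). Baseline characteristics are to be summarised by arm; nothing says that they enter the model. The secondary outcomes are to be modelled in the same way.

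Both omitted variables are part of the design. Under Data collection: "Data collection of patient outcomes are at baseline (T0) (directly after inclusion of a patient in the study"), and the RMDQ is one of those patient outcomes. Under Randomisation, allocation procedure and blinding: "Randomisation is stratified for number of GPs working in the primary care practice (one or two vs more than two"), with the stated aim of similar patient numbers in the two arms.

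**The concern.** For a persistent complaint, the patient's own starting score is usually the best available predictor of the later score. The Discussion itself relies on the chronic nature of the pain to justify before-after comparisons. A comparison of follow-up scores alone leaves that predictor unused, so the standard error is larger than it need be. Any baseline difference between arms also passes, in proportion to the correlation, into the estimate.

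The design makes such differences harder to rule out. Whole practices are allocated. The recruitment section speaks of practices already randomised when patients are approached. Patients and GPs are not blinded. The effect is expected only in the roughly half of patients who are rule-positive, which leaves a smaller effective sample in which to balance.

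At stake are the width of the interval around the main result and its credibility if the baseline table shows the arms to differ.

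**Working it through.** **Inputs from Sample size:** difference 2.5; SD 6.0; two-sided alpha 0.05; power 0.80; about 50% rule-positive; ICC 0.05; 16 patients per practice; 25% loss.

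**Assumed, not in the article:** correlation r between T0 and 4-month RMDQ of 0.3, 0.5 or 0.7; the same r at patient and practice level; equal SDs at both times.

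**1. The plan's own figure.** n per group = 2 × (1.96 + 0.842)² × 6.0² / 2.5² = 90.4, so 91 per group and 182 in all. The article's 180 fits as the total of both groups, although it is labelled per group, and the later steps use it as a total: 180 × 2 = 360 (for 50% rule-positive); 360 × 1.75 = 630; 630 / 0.75 = 840. The figure of 840 therefore reproduces, with no allowance for a baseline covariate.

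**2. Current model at 840 enrolled.** Analysed: 840 × 0.75 = 630, or 315 per arm, of whom 157.5 are rule-positive. Effective number per arm = 157.5 / 1.75 = 90. SE = 6.0 × √(2/90) = 0.894. Power = Φ(2.5/0.894 − 1.96) = 79.8%.

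**3. With baseline RMDQ added.** The variance is multiplied by 1 − r².

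| r | variance factor | reduction | SE | power | enrolment for the original power (840 × factor) |
|---|---|---|---|---|---|
| 0 | 1.00 | 0% | 0.894 | 79.8% | 840 |
| 0.3 | 0.91 | 9% | 0.853 | 83.4% | 764 |
| 0.5 | 0.75 | 25% | 0.775 | 89.8% | 630 |
| 0.7 | 0.51 | 49% | 0.639 | 97.5% | 428 |

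**4. Chance imbalance.** With SD 6.0 at baseline too, the difference in baseline means between rule-positive arms has SE 0.894 and a 95% range of ±1.96 × 0.894 = ±1.75 points. A difference of at least 1 point in either direction has probability 2 × (1 − Φ(1/0.894)), about 26%. A 1-point difference shifts the unadjusted 4-month contrast by r × 1 = 0.3, 0.5 or 0.7 points, which is 12%, 20% or 28% of the 2.5-point target.

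**5. Sensitivity to the design effect.** The value 1.75 counts all 16 patients in a practice, but only about 8 would be rule-positive. With 8, the design effect is 1 + 7 × 0.05 = 1.35. The unadjusted SE is then 0.786 and power 88.9%, rising to 91.6%, 95.7% and 99.4% at r of 0.3, 0.5 and 0.7. A small simulation of the mixed model (40 practices of 16, ICC 0.05, 120 runs per r) agrees: the average model SE fell from about 0.78 to 0.74, 0.68 and 0.57. The proportional saving in variance does not depend on the design effect, but the gain in power is smaller when power is already high.

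**6. The stratum.** If it explains a share q of the between-practice variance, the design effect becomes 0.95 + 0.80 × (1 − q). For assumed q of 0, 10% and 25% this is 1.75, 1.67 and 1.55, giving power of 79.8%, 81.6% and 84.4%. In the simulation a stratum with no prognostic effect left the SE essentially unchanged.

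**The case against.** The strongest reply is that nothing is broken. Under randomisation the unadjusted model is valid, its standard error already covers chance imbalance, and the sample size was worked out for that model. What is lost is power above the 80% target. This stands, and it sets the weight of the point.

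A second reply is that the verb include need not close the list, and that covariates are often left to an analysis plan, which is not shown here. This carries less weight. The article itself names the fixed effects, the interaction and the random intercept, and nothing elsewhere in it adds a covariate.

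Third, the size of the gain is assumed. The article says only that the complaints are chronic and gives no correlation; at r = 0.3 the gain is under 4 percentage points of power. That is why the range starts there.

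Fourth, T0 is not a perfect baseline. It is a questionnaire sent after the eligibility call and chased by reminders, telephone and post, so it cannot be taken as available for every patient. The Intervention section does not say when the rule-outcome letter goes out relative to it, so some forms may be completed after the advice is known. This stands too, and it has to be dealt with in the fix.

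**Conclusion.** The point holds as one of precision and of protection against chance imbalance. At the planned 840 enrolled, adding baseline RMDQ would reduce the variance of the effect by 9% to 49% and raise power from 79.8% to between 83.4% and 97.5%. This assumes r of 0.3 to 0.7, equal at patient and practice level, and the article's design effect. With a design effect based on rule-positive patients only, power starts at 88.9% and there is less to gain. The shift of 0.3 to 0.7 points per point of baseline difference further assumes equal SDs at T0 and 4 months.

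Two stronger readings are tempting, and the article supports neither.

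- A reader might infer that the planned estimate is biased. Chance imbalance is random error that the standard error already reflects. Bias would need recruitment to differ by allocation, and the article says recruitment is the same in both arms.
- A reader might infer that omitting the stratum makes the standard errors wrong by a material amount. The stratum was chosen to even out patient numbers, and the article gives no evidence that practice size predicts RMDQ. Its gain could be nil. It belongs in the model so that the analysis follows the randomisation.

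**What to change.** Before analysis, and ideally before anyone sees outcome data by arm:

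- Add baseline RMDQ (continuous) and the practice-size stratum as fixed effects in the primary model, alongside allocation, rule result, their interaction and the practice random intercept.
- Add the matching baseline score, and the stratum, to the models for the continuous secondary outcomes.
- State how a missing T0 score is handled, for example by simple imputation of the baseline covariate that uses neither allocation nor the 4-month score, so that no patient drops out of the analysis for want of a baseline value.
- Identify T0 questionnaires completed after the rule-outcome letter and examine their influence in a sensitivity analysis. The time at which the letter is sent need not change.

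The cost is a short addition to the model specification, one rule for missing baselines and one sensitivity analysis. It needs no extra patients and no new questionnaires. The dates of T0 completion and of the letter must be available for the last item.

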A weakness of the study is that the contrast between intervention and control groups disappears after 4 months, as patients of the control group are also provided with the advice of the referral strategy. Nevertheless our primary outcome is assessed before the contract between intervention and control group is eliminated. We expect that 4 months is a sufficient period to achieve a substantial improvement in the primary outcome by using the referral strategy in the intervention group. For other outcomes we can use a before after design within patients which is acceptable as the back pain complaints are chronic. Another potential weakness is that patients are selected by a registry, rather than only actively care seeking patients are invited to participate. This can lead to a lower participation rate of the invited patients and a potential selection bias of only severe cases of low back pain. However in the prior CaFaSpA studies, the same approach to select participants by the GP register was conducted and this didn’t result in a more severe low back pain study population [4, 5]. In both CaFaSpA studies was the VAS pain comparable with other low back pain cohorts. One last limitation of this study is that the intervention i.e. the CaFaSpA referral rule is applied by research assistant not by GPs themselves, this pragmatic approach can influence the outcomes of the study. We have chosen for this pragmatic approach as GPs pointed before the start of study that it is often too busy during consultation hour to properly ask the questions of the referral rule and that the application of the referral rule would not be uniform but heavenly time dependent.

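### The long-term trajectories model has only a patient random intercept, so it cannot describe individual change, and its standard error for a linear time effect is too small if patients' slopes differ

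*Protocol article*

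**What the plan says.** The Data analysis section of the protocol article explains that controls also receive the referral advice after 4 months. It gives up the arm comparison for later visits: "Contract between the intervention and control group is no longer present" (the first word is evidently a misprint for contrast). In its place, "individual trajectories will be modeled using random effect regression with patient outcome as the dependent variable and time as covariate and a random intercept for" the patient. No random slope, residual correlation structure or robust standard error is named. The article does not say whether time is linear or categorical.

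The Discussion relies on the same within-patient comparison: "For other outcomes we can use a before after design within patients which is acceptable as the back pain complaints are chronic".

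The Data collection section schedules assessments at baseline and "after 4 months (T1), after 12 or 16 months (T3) and after 24 or 28 months (T4"). The later month in each pair belongs to the control arm, for which the Control group section says "this will be sixteen and twenty-eight months after inclusion of the study". The significance threshold is general: a p-"value of <0.05 will be considered statistically significant".

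On whether patients' courses should differ, the Data analysis section gives the reason for its interaction term: "As the effect of the referral strategy is expected in the subgroup of patient with a referral advice". The Sample size section puts that subgroup at around half of participants.

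**The concern.** A model with only a patient intercept lets patients differ in level but never in change. It also treats two assessments 4 months apart as no more alike than two that are 24 months apart. That conflicts with the stated aim of modelling individual trajectories, and it sits badly with the protocol's own expectation that only part of the sample will benefit.

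There is also an inferential cost. Real variation in slopes is absorbed into the residual variance, and only part of it reaches the standard error of the mean time effect. Confidence intervals for long-term change are then too narrow. Within-patient change is the only long-term evidence on patient-reported outcomes that the design leaves.

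**Working it through.** **The plan's own figure.** There is none for this model. The stated sample size concerns the 4-month comparison and plays no part here.

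**Inputs from the article.** Visits at 0/4/12/24 months (intervention) and 0/4/16/28 months (control); random intercept only; threshold 0.05, taken as two-sided in line with the Sample size section ("using a two-sided α of 0.05 and power of 0.80"); total RMDQ SD 6.0; planned difference 2.5 points; about 50% with a positive rule.

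**Assumed, because the article does not give them.** Residual SD s of 2, 3 or 4 points; slope SD τ, expressed in points per 24 months; linear time; model-based standard errors.

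**Step 1, time sum of squares.** For 0/4/12/24 the mean is 10, so Sxx = 100 + 36 + 4 + 196 = 336. For 0/4/16/28 the mean is 12, so Sxx = 144 + 64 + 16 + 256 = 480. Four visits leave 3 within-patient degrees of freedom.

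**Step 2, true and reported variance.** With complete data on one schedule, the variance of one patient's estimated slope is s²/Sxx + τ². The intercept-only model estimates its residual variance as s² + τ²·Sxx/3 and therefore reports s²/Sxx + τ²/3. With r = τ²·Sxx/s²:

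ratio true/reported = (1 + r)/(1 + r/3), which cannot exceed 3.

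Actual rejection rate = 2·[1 − Φ(1.96/√ratio)].

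**Step 3, one case in full.** Take s = 3 and a slope SD of 4 points per 24 months. Then r = (4/24)²·336/9 = 1.037, the ratio is 2.037/1.346 = 1.514, its square root is 1.230, and 1.96/1.230 = 1.593, so rejection is 11.1%.

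**Step 4, the range at 0/4/12/24 months.**

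| Slope SD (points per 24 months) | s = 2 | s = 3 | s = 4 |
|---|---|---|---|
| 0 | 5.0% | 5.0% | 5.0% |
| 1.25 | 6.7% | 5.8% | 5.4% |
| 2 | 8.9% | 6.9% | 6.1% |
| 3 | 12.2% | 8.9% | 7.3% |
| 4 | 15.2% | 11.1% | 8.9% |
| 6 | 19.4% | 15.2% | 12.2% |

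At the limiting ratio of 3, 1.96/√3 = 1.132 and rejection is 25.8%. On the control schedule with s = 3, slope SDs of 3, 4 and 6 give 10.2%, 12.8% and 17.1%.

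**Step 5, what the protocol's own figures imply.** If half the patients change by the planned 2.5 points and half by 0, the SD of change is 2.5·√(0.5·0.5) = 1.25. Treating this as the slope SD per 24 months is itself an assumption, since 2.5 points is a 4-month difference between groups. It corresponds to 5.8% at s = 3.

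**Step 6, simulation with fitted mixed models.** The runs used 400 patients, 800 replicates per scenario, s = 3 and no true mean change; the Monte Carlo standard error near 5% is about 0.8 percentage points. On the common 0/4/12/24 schedule without dropout, the intercept-only model rejected 4.6%, 6.8%, 8.5%, 11.1% and 14.3% for slope SDs of 0, 2, 3, 4 and 6, in line with the formula. With slope SD 4 and 25% dropout it rejected 9.9%; with both schedules mixed as well, 14.5%. Adding a random slope gave 4.3% to 5.6% on the common schedule. It gave 6.6% with mixed schedules and dropout, about two Monte Carlo standard errors above 5%.

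**Step 7, categorical time.** Under the intercept-only model the overall 3-df test stayed at 4.1% to 6.5%. The single contrast of last visit against baseline reached 13.8%.

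**The case against.** The strongest objection is about size. A reader might infer that the test rejects two to three times too often. The documents do not support that as a general statement, because they give neither a slope SD nor a residual SD. Rejection of 10% to 15% needs r between 0.80 and 2.23, which at s = 3 means a slope SD of about 3.5 to 5.9 points per 24 months. The one source of differing courses that the protocol quantifies gives about 6%. Larger spread is plausible in chronic back pain but is an assumption. The full range is 1.0 to 5.2 times nominal (25.8/5). This part of the objection stands.

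A reader might also infer that a false finding of improvement becomes likely. It does not. The rates are two-sided, and under a zero mean change only half the rejections point to improvement: about 5.5% when the total is 11%, and 13% at the limit. Moreover, if some patients improve and the rest do not change, the mean change is not zero and a rejection is not a false positive. The interval would still be too narrow in that case.

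Third, this is a condensed article. Time coding and the type of standard error may be settled in an analysis plan that is not shown, and with an overall test of categorical time there is almost no inflation. That stands as a condition on the numbers. It does not remove the point, because the article does state the random part.

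Finally, the analysis is secondary and uncontrolled, and the Discussion already names the lost contrast as a weakness. That limits the consequence.

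**Conclusion.** The point holds in a limited form. That an intercept-only model forces parallel courses, and so cannot describe individual trajectories, follows from the stated specification and rests on no assumed number. That its standard error is too small when slopes vary follows algebraically for linear time with model-based errors, and the simulations show the same for a last-visit-versus-baseline contrast.

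The amount is conditional: little above nominal if slopes vary only as much as the protocol's own figures imply, and clearly inflated only for moderate to large slope spread. The 4-month primary RMDQ comparison uses a different model and is untouched. This is a cheap improvement, not a flaw that threatens the trial's main conclusion.

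**What to change.** In the Data analysis section, specify for the long-term model a random intercept and a random slope for time per patient, with unstructured covariance between them. An unstructured residual covariance across the assessments is an alternative; because the arms are seen at different months after T1, it would need to be defined separately by arm. State that long-term confidence intervals and p-values come from that model.

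The cost is a one-line change to the model specification, a slightly more complex fit and no new data. Standard errors grow only as far as slopes vary. At s = 3 on the 0/4/12/24 schedule, the square root of the ratio in Step 2 implies about 3% for a slope SD of 1.25 and about 23% for a slope SD of 4. If slopes hardly vary, the slope variance is estimated near zero and the result is practically unchanged.

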**Methods/Design:**

This study design is a cluster randomized controlled trial with GP as clusters. GPs throughout the Netherlands are invited to participate and randomized to either the intervention or the control group. Patients from participating GPs are invited to participate if they have ever been registered with low back pain, without radiation (ICPC L03) and aged 18–45 years. To be included in the study, patients need to have current low back pain and chronic low back pain (>12 weeks). In the intervention arm a referral strategy for axSpA will be applied in CLBP patients, in the control arm care as usual will be provided for CLBP patients. The referral strategy consists of four easy to use variables. All are questions about the back pain complaints of the patients. Data is prospectively collected in an online database at baseline (T0), 4 months (T1), 12 months (T2) and 24 months (T3). After time point T1 (4 months) patients from the control group will also receive the intervention i.e. the application of a referral strategy for axSpA. The effect of the referral strategy is measured at three different levels, by patient outcomes (e.g. pain scores, quality of life), process measures (e.g. number of axSpA diagnoses by rheumatologists) and by costs (work productivity and health care resources use). Our primary outcome is the Roland Morris Disability Questionnaire after 4 months, secondary outcomes are pain and quality of life. Costs will be assessed before and after the use of the referral strategy, to estimate if the use of the strategy will lead to a reduction in health care costs and improvement in work participation.

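### The long-term model has time as its only covariate, so change at 1 and 2 years cannot separate the referral strategy from natural course and regression to the mean

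*Protocol article*

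**What the plan says.** The Data analysis section first gives the aim: "We intended to assess the effect of using the referral strategy also at 12 and 24 months". It then notes that controls also receive the rule outcome after 4 months and, for that reason, turns to modelling each patient's course by "random effect regression with patient outcome as the dependent variable and time as covariate and a random intercept for patient". The 4-month model in the same section is listed term by term: allocation, rule result, their interaction, and a random intercept for practice. None of these is named for the long-term model.

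The Discussion concedes as a weakness that "the contrast between intervention and control groups disappears after 4 months". Shortly afterwards it says: "For other outcomes we can use a before after design within patients which is acceptable as the back pain complaints are chronic".

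On timing, the Control group section schedules the controls' later visits at 1 and 2 years after they receive the rule outcome and adds that "this will be sixteen and twenty-eight months after inclusion of the study". The Data collection section gives 12 or 16 and 24 or 28 months. The abstract gives one schedule for everyone: "Data is prospectively collected in an online database at baseline (T0), 4 months (T1), 12 months (T2) and 24 months (T3").

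**The concern.** A coefficient for time estimates how patients change on average. Without a comparison or an exposure term it cannot say why they change. Three causes are mixed here: the strategy, the natural course of back pain, and regression to the mean in people who had to have back pain at the moment they entered.

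Chronicity does not remove the last two. A chronic complaint can still fluctuate, and a requirement for current pain tends to pick patients at a worse point of that fluctuation.

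The model also averages over patients in whom the protocol itself expects no effect. The Sample size section says that rule-negative patients in the intervention arm get the same treatment as usual care, so that an effect can be assessed only in rule-positives.

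At stake is what the trial may conclude at 1 and 2 years about disability, pain and quality of life. An improvement that would have happened anyway could be presented as a benefit of the strategy.

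**Working it through.** **1. Exposure by visit**, from the Control group and Data collection sections. The rule outcome is taken as communicated at about inclusion in the intervention arm.

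| Arm | Months since inclusion | Months since rule outcome communicated |
|---|---|---|
| Intervention | 0, 4, 12, 24 | 0, 4, 12, 24 |
| Control | 0, 4, 16, 28 | not yet, 0, 12, 24 |

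If time runs from inclusion, month 4 combines patients with 4 months of exposure and patients with none under one time effect. If it runs from communication, the controls' baseline lies at minus 4 months. The article does not say which is meant. In either case the controls' first 4 months are the only unexposed period after inclusion, and the stated model does not set them apart.

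**2. The plan's own figure.** The calculation disputes no figure but uses the plan's number of completers: 360 × 1.75 = 630, and 630/0.75 = 840 to enrol. Both reproduce from the plan's 360.

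**3. How small a drift is called significant.** Inputs: 630 completers and SD 6.0 (Sample size section). The within-patient correlation ρ is not in the documents; 0.4 to 0.8 is assumed. The plan does not say that 630 patients remain at 24 months, so that is an assumption too.

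SE of mean change = 6 × √(2(1−ρ)/630)

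- ρ = 0.4: SE = 0.262; p<0.05 from 1.96 × 0.262 = 0.51 points
- ρ = 0.8: SE = 0.151; p<0.05 from 1.96 × 0.151 = 0.30 points

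For an assumed natural improvement of 1 point and ρ = 0.6, SE = 0.214 and the chance of significance is Φ(1/0.214 − 1.96) = 0.997.

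**4. Simulation with no strategy effect** (40 practices of 16 patients, ICC 0.05, ρ = 0.6, natural improvement of 1 point, 1,500 trials). The before-after estimate averaged −1.0 point and was significant in 99.7% of trials. The randomised arm contrast in change at 4 months, analysed on practice means, averaged 0.0 and was significant in 6.1%.

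**5. Regression to the mean, illustration only.** Suppose entry keeps the worst fraction q of a normal distribution with SD 6 (φ is the normal density, z the cut-off). Expected fall = (1−ρ) × 6 × φ(z)/q.

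- q = 0.9, ρ = 0.8: 0.2 × 6 × 0.195 = 0.23 points
- q = 0.5, ρ = 0.5: 0.5 × 6 × 0.798 = 2.4 points

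The planned effect is 2.5 points. The range is wide because q and ρ are both assumed. Entry is by current pain, not by an RMDQ threshold, so the true value cannot be derived from the documents.

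**6. Pooling.** About 50% of patients are expected to be rule-positive. If a 2.5-point effect is confined to them, the pooled average is 0.5 × 2.5 + 0.5 × 0 = 1.25 points, on top of whatever drift is present.

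**7. Practice effect.** In one simulated data set the time coefficient was −1.141 with SE 0.208, both with and without a practice intercept. With no drift and a constant practice effect, the patient-only model rejected in 4.7% of trials. Rejection rises only if change itself varies between practices: with an assumed between-practice SD of change of 1.0 point it was 12.8%. The approximation agrees: the variance of the mean change is 28.8/640 = 0.045 within practices plus 1.0/40 = 0.025 between them, and 2[1 − Φ(1.96 × √(0.045/0.070))] = 0.12.

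**The case against.** Several points on the other side stand.

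- The article admits the lost contrast and, in Data analysis, speaks of modelling patients' courses rather than of estimating an effect. That the result will be read as an effect is therefore an inference. It is a reasonable one, because the model replaces an intended effect assessment and the Discussion calls the before-after reading acceptable, though only for unspecified other outcomes.
- The 16- and 28-month control visits are deliberate. They align time since exposure between the arms and are not an error.
- Patients come from a register and not only from active care seekers, and the Discussion reports that the same approach gave no more severe a population in earlier studies. This limits what can be said about size. It compares cohorts with each other, however, and does not show that a patient's score is stable after entry. The criterion remains that "patients need to have current low back pain and chronic low back pain (>12 weeks").
- Only 0 to 4 months is unexposed, and the randomised analysis already uses that contrast. A richer model thus gains less at 1 and 2 years than it may seem.

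The argument that covariates belong in an unseen analysis plan carries less weight. The article states this model and its justification, and it lists the terms of the 4-month model in full.

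A reader might also infer that leaving out the practice intercept causes the misreading or makes the time estimate falsely precise. The 4-month model does have that term: "This random intercept stand for the effect of different primary care practices (i.e. clusters"). But a constant practice effect is absorbed by the patient intercept, and step 7 shows the time estimate and its SE unchanged. The stated long-term model contains no between-arm contrast to which a between-arm inflation could apply. A practice term for change over time is a secondary matter, relevant only if change differs between practices.

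**Conclusion.** The concern holds for the long-term analysis. As written, the time coefficient cannot distinguish the strategy from natural course or regression to the mean, and it averages over rule-negative patients in whom the protocol expects no effect. The chronicity argument does not repair this.

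How large the distortion would be is unknown. The calculations show only that, under the assumed correlations and 630 completers, a drift of 0.30 to 0.51 points is enough for significance, and that regression to the mean could be anything from negligible to about the size of the planned effect. A reader might infer that long-term results are certain to be biased toward benefit. That direction is plausible given entry on current pain, but the documents do not establish it.

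The randomised 4-month primary analysis is not affected. The change should be made, but the point does not threaten the trial's main result.

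**What to change.** 1. State whether time runs from inclusion or from communication of the rule outcome. Bring the abstract into line with the Control group and Data collection sections, including the visit labels (T2 and T3 in the abstract, T3 and T4 in Data collection).
2. Model time since inclusion plus a time-varying exposure term (time since the rule outcome was communicated), with the rule result and its interactions with time and with exposure. The control arm's first 4 months then inform the unexposed course.
3. Report change at 1 and 2 years as descriptive, or as dependent on stated model assumptions, and not as an effect of the strategy. Remove the justification that a before-after design is acceptable because complaints are chronic.
4. As a secondary check, allow change over time to vary between practices.

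The cost is revised wording and a somewhat larger model; no new data are needed. The downside is that beyond 4 months both arms are exposed, so exposure effects there depend on the assumed shape of the time and exposure terms. The report should say so.
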